### Analytic Strategy: Reach, Adoption, and Implementation

We will assess reach by presenting descriptive statistics of the 8 clinics in the trial and comparing demographic characteristics (sex, race, and ethnicity) between patients using the app versus the overall clinic population using chi-square tests. We will assess factors of patient adoption using logistic GEE models (outcome: any meaningful use each week) and Poisson or negative binomial GEE models (outcome: days of meaningful use per week). Predictors of adoption will include patient sociodemographic factors (age, race and ethnicity, gender, sexual orientation, SUD history) and time-varying factors based on measures collected through weekly and semiannual surveys. Adoption will also be examined as a predictor of individual-level effectiveness outcomes for patients who enroll in the app using logistic GEE models (outcomes: viral nonsuppression and missed visit). Models will account for repeated measures using hierarchical clustering for repeated observations from patients within sites.

Interview and focus group data will be recorded and transcribed. Transcripts will be independently coded by 2 members of the research team, who will meet to discuss and resolve any significant coding inconsistencies. We will manage and analyze qualitative data using NVivo (Lumivero). We will use qualitative analysis to assess adoption at the staff level and use this information to understand potential differences in outcomes between sites related to reach, effectiveness, and implementation outcomes.

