### Clinic-Supported Intervention Components

While the Connections app is available to the full clinic population, more intensive support involving digital health–enhanced, person-centered care coordination can only be delivered to a subset of patients due to staffing and other resource limitations. To maximize the potential impact of the ART-C intervention, the research team consulted with Vivent Health leadership to develop the eligibility criteria provided in Textbox 1 for the clinic-supported arm of the intervention.

Our target study population involves people at risk of viral nonsuppression and lapses in HIV care due to current or past substance use and history of disruptions to HIV care engagement or viral suppression, which align with these criteria.

Inclusion and exclusion criteria.

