### Data Collection

We will use the RE-AIM model to guide our overall evaluation of implementation. RE-AIM is a comprehensive framework that assesses 5 dimensions: reach, effectiveness, adoption, implementation, and maintenance [45].

The primary “reach” measure will be the percentage of Vivent Health patients with HIV who have downloaded and used ART-C, along with their sex, racial, and ethnic characteristics. The primary “effectiveness” outcomes (missed HIV care visits and viral nonsuppression) will be evaluated from clinical EHR data documenting HIV viral load results and the status (attended and missed) of scheduled HIV care visits. We will also describe Connections app use and collect quarterly surveys from patients in the clinic-supported intervention. “Adoption” at the patient level is based on research-driven metrics of meaningful use for mHealth, defined as a patient accessing any part of ART-C beyond the home page during a given week in the 12-month period after downloading the app [46].

“Implementation” will be evaluated based on fidelity to key components of ART-C at the clinic level, using quantitative and qualitative methods. We will define fidelity in two dimensions: (1) the amount of the intervention received (ie, use of the dashboard) and (2) the quality of intervention delivery (ie, the intervention participant’s reflections on their experience using the dashboard and the effect it had on their approach to care delivery). “Maintenance” will be defined as follow-up on the effectiveness measures (viral load and missing visit rates) in the 6-month postintervention period.

Using qualitative interviews, we aim to gain rich insights into implementation and adoption processes at various sites from a diverse set of stakeholders involved in implementation. Data will be coded, and the analysis will help us refine the Connections app for future dissemination by determining individual and organizational conditions necessary to promote effectiveness. Interviews will be conducted with multilevel stakeholders, including study participants (10 to 20 interviews), clinic staff identified as change leaders (5 to 10 interviews), and the peer mentors (5 interviews).

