Power and sample size calculations will be based on the study by Hemming and Taljaard [49]. For a stepped-wedge design with 8 clusters stepped in 1 to 2 clusters at a time over 5 time periods and an assumed intraclass correlation coefficient of ρ=0.10, the design effect relative to an individual-based randomized controlled trial is 3.0. Preliminary data suggest the percentage of enrolled patients with nonsuppressed viral load (HIV RNA ≥200) before intervention to be 26.7%. On the basis of consultation with clinic leadership and pilot data from a single site, we assume a meaningful effect size to be a 10 percentage point reduction in nonsuppressed HIV RNA tests in the study sites after intervention, to 16.7%. The 8 clinical sites average 526 active patients per site per year for an estimated total of 4208 potential patients. We aim to reach approximately 15% of clinic patients using patient engagement strategies geared toward helping those patients most likely to benefit from the clinic-supported intervention. We hypothesize that the implementation strategy can effectively reach 631 (15%) patients and achieve a 68% improvement in viral load suppression among this highly vulnerable population. On the basis of these assumptions, with 3682 active patients, our power to detect a 10 percentage point reduction in nonsuppressed viral loads will be 98.5% (1–β=.985). The study will be sufficiently powered (>80%) to detect up to a 7 percentage point reduction in patients with nonsuppressed viral load.

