## Results

In the 2 years before starting ART-C implementation (December 2021 to November 2023), 6710 patients received HIV-related services, including a laboratory test or scheduled visit. After excluding patients who never attended a medical visit, died before the time of study approval, or did not speak English, the resulting sample included 6035 (89.94%) patients who received HIV care in 1 of the 8 participating clinics.

Demographic and clinical characteristics of patients in the baseline sample are provided in Table 1. The majority (75%-88%) of patients at all clinics described their gender as men. The mean age of the patients as of December 2021 ranged from 41.7 (Kansas City) to 48.7 years (Denver). Self-reported race varied geographically. African American and Black individuals comprised the majority of patients in the Milwaukee and St Louis clinics, while most patients in the other 6 clinics reported as White individuals. Hispanic ethnicity was least common in St Louis (60/1409, 4.26%) and most common in Austin (210/754, 27.9%). The prevalence of SUD among active patients ranged from 4.2% (13/307; Kansas City) to 37.4% (82/219; Kenosha).

Table 2 displays the results of the baseline analysis of the 2 main study outcomes, providing the baseline level of HIV care indicators to which future, postintervention results will be compared. Over the 2 years before trial inception, patients had a mean of 4.1 to 7.8 scheduled care visits across sites, and 45% to 70% of them missed 1 or more visits. Patients had an average of 2.2 to 4 HIV RNA tests, and 14% to 37% of them had at least 1 nonsuppressed (>200 copies/mL) HIV RNA test. Multimedia Appendix 1 provides additional patient characteristics, such as HIV transmission route, sexual orientation, employment, and other features of the patient population at the clinic.

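### The reach analysis tests app users against a clinic population that contains them, which makes the chi-square test conservative for demographic gaps in uptake

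*Protocol article*

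**What the plan says.** Under Analytic Strategy: Reach, Adoption, and Implementation, the article says that reach will be assessed with descriptive statistics for the 8 clinics and by comparing sex, race and ethnicity "between patients using the app versus the overall clinic population using chi-square tests".

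Two other places show that users belong to the comparator. Data Collection defines reach as "the percentage of Vivent Health patients with HIV who have downloaded and used ART-C", so users are the numerator of a fraction whose denominator is the clinic population. Clinic-Supported Intervention Components says: "While the Connections app is available to the full clinic population". Nowhere does the article take users out of the comparator or adjust for the overlap.

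The only uptake figure is in the power paragraph of Analytic Strategy: Effectiveness and Maintenance: "The 8 clinical sites average 526 active patients per site per year for an estimated total of 4208 potential patients", followed by "We hypothesize that the implementation strategy can effectively reach 631 (15%) patients". That target is tied to the clinic-supported level of the intervention. It is not a forecast of total app use.

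**The concern.** A chi-square test of two groups takes them to be separate and independent. Here every app user is also a member of the comparison group. Two things follow. The observed contrast is diluted, because users are compared partly with themselves. The standard error is also too large, because it ignores the positive covariance between the two proportions. Both push the statistic towards zero.

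The Discussion rests part of the trial's rationale on persistent disparities by race, ethnicity and socioeconomic status, and reach is one of the five RE-AIM dimensions. In a check for unequal uptake, lost sensitivity makes a real gap easier to miss, and the loss grows as more patients use the app.

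**Working it through.** **Inputs**
- Clinic population N: 8 × 526 = 4208 (power paragraph).
- Illustrative users n: 0.15 × 4208 = 631.2, which reproduces the stated 631. Non-users: 4208 − 631 = 3577.
- Base share p: Table 1 gives 798 + 203 + 41 + 741 + 213 + 85 + 42 + 129 = 2252 Black patients. The site columns sum to 6032 (the table header gives 6035), so p = 2252/6032 = 37.3%.
- Assumed, because not stated: two-sided alpha of 0.05; app-use fraction r of 5%, 15% or 30%; patients otherwise homogeneous.

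**Step 1: the contrast.** The overall share is r × p_users + (1−r) × p_nonusers. Hence p_users − p_overall = (1−r)(p_users − p_nonusers). At r = 0.15, a 5-point gap appears as 0.85 × 5 = 4.25 points.

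**Step 2: the variance.** With n = rN, the true null variance of p_users − p_overall is p(1−p)(1−r)/n.
- Two-column test, users counted twice: it uses p(1−p)(1/n + 1/N) = p(1−p)(1+r)/n. Relative to a correct z, its z is multiplied by √((1−r)/(1+r)).
- Goodness-of-fit test, clinic shares taken as known: it uses p(1−p)/n. Its z is multiplied by √(1−r).

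**Step 3: true size.** Rejection needs a correct |z| above 1.96 divided by the factor.

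| r | Two-column: factor, cut-off, size | Goodness-of-fit: factor, cut-off, size |
|---|---|---|
| 5% | 0.951, 2.06, 3.9% | 0.975, 2.01, 4.4% |
| 15% | 0.860, 2.28, 2.3% | 0.922, 2.13, 3.4% |
| 30% | 0.734, 2.67, 0.8% | 0.837, 2.34, 1.9% |

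Simulation at 15% agrees for the two-column form: about 2.2%, against 5.0% for users versus non-users.

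**Step 4: power at r = 15%.** Users versus non-users has 80% power when the expected z is 1.96 + 0.84 = 2.80. The planned test then has power Φ(2.80 − 2.28) = 70% in two-column form and Φ(2.80 − 2.13) = 75% in goodness-of-fit form. The losses are about 10 and 5 points.

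**Step 5: worked example.** Take 209 of 631 users (33.1%) and 1362 of 3577 non-users (38.1%) as Black, which is 1571 of 4208 overall (37.3%).
- Users versus overall, two-column: chi-square 4.19, p = 0.041.
- Users versus overall, goodness-of-fit: chi-square 4.78, p = 0.029.
- Users versus non-users: chi-square 5.63, p = 0.018.

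**The case against.** - **The table layout is inferred.** The article gives one condensed sentence and does not say that users are counted in both columns. That is fair, and the goodness-of-fit reading roughly halves the power loss at 15%. It does not remove the problem, since the test is conservative under either reading. A user/non-user table may be what is intended, but the article names a different comparator.

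- **The null is the right one and the error is on the safe side.** Users match the overall population exactly when they match non-users, so the overlap produces no false claim of disparity. This stands. A reader might infer from the broken independence assumption that significant results cannot be trusted. The algebra shows otherwise: what is lost is sensitivity.

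- **The 15% is borrowed.** It is a target tied to the clinic-supported level. Total app use could end higher or lower. This stands, and is why a range is shown.

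- **Site mix may dominate.** In Table 1 the Black share runs from 14% (Denver) to 54% (Milwaukee). If uptake differs by site, a pooled test can reject often with no gap inside any clinic. Simulations that assumed varying site uptake showed this for the planned test and, more often, for users versus non-users. It is therefore tempting to read 2.3% as the size that the test would have in this trial, or to conclude that the reach analysis as a whole leans towards finding equal uptake. The documents support neither.

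- **User data may be incomplete.** Under Intervention Overview, patient-directed users share no individual-level data with researchers. If some users cannot be identified, the non-user group will contain them. But the planned test already needs users' demographic counts, so the change asks for nothing beyond that.

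**Conclusion.** The point holds as a flaw in the stated comparison. Users are a subset of the comparator, the contrast shrinks by (1−r), and the test is conservative under both plausible forms. The loss is small at low uptake, moderate at 15% and larger beyond that. These sizes rest on homogeneous patients, a 5% two-sided level and assumed values of r, none of which the article fixes. They isolate the effect of the overlap and do not predict how the test will behave across eight differing clinics.

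The primary reach measure, a percentage of patients, is untouched. So are the effectiveness outcomes, missed visits and viral nonsuppression.

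**What to change.** In Analytic Strategy: Reach, Adoption, and Implementation, apply the chi-square tests to app users versus clinic patients not using the app. Obtain non-user counts as the clinic total minus users, from the same demographic counts that the planned test already needs. Keep users versus the overall clinic population as a descriptive display without a p-value.

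The cost is one sentence of wording, with no new patients or procedures. Data collection is expected to run to 2027, so the change can precede the analysis. It removes the overlap only. It does not deal with differences in case mix between sites or with users who cannot be matched to clinic records.

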### The Need for Just in Time Strategies for Monitoring and Responding to Social Determinants of Health in HIV Care Settings

While clinical factors, such as antiretroviral adherence [14] and retention in care [15] are well understood to be proximal determinants of viral suppression, nonclinical factors, such as poverty [16], lack of health insurance [17], homelessness [18], food insecurity [19], and criminal justice involvement, also influence HIV care outcomes. In 1 community-based cohort study of predominantly African American people with HIV who inject drugs, participants who achieved viral suppression after initiating ART had a 1-in-4 risk of experiencing viral rebound (ie, virologic failure) during any 6-month interval [20]. In that study, loss of viral suppression was more common if participants reported recent incarceration, daily injection drug use, or homelessness, demonstrating how time-varying social and behavioral factors can signal vulnerability to treatment interruptions Other patient-level factors that have been consistently correlated with treatment interruptions include depression and anxiety [21], low self-efficacy, internalized HIV-related stigma [22], and inadequate social support [23].

A major challenge to addressing HIV-related health disparities is the tendency for patients to miss appointments during periods of greatest vulnerability. Research using electronic health record (EHR) data shows that treatment failure is predictable based on individual-level characteristics documented in the EHR [24,25]. However, the social, behavioral, and structural factors that increase the risk of treatment disruption and require the timely provision of support to ensure care retention are not typically captured in EHRs. Therefore, health care providers do not generally have timely access to data that would help them provide support when it is most needed. As a result, most disruptions in ART are detected only after a lapse in care has already occurred. The fact that previous treatment disengagement and virologic nonsuppression are 2 strong predictors of future care disengagement [24,25] further underscores the need to interrupt the cycle of treatment disruption and find new ways to support retention.

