### Study Outcomes

We defined 2 study outcomes using EHR data, which will be examined at the clinic level and continually assessed during pre- and postimplementation periods. The first outcome, missed clinic visits, is defined as the proportion of appointments scheduled with an HIV care provider that a patient failed to attend and did not call in advance to cancel or reschedule. The second outcome, viral nonsuppression, is defined as the proportion of patients with an HIV RNA test result greater than the lower limit of detection (200 copies/mL) among those who received 1 or more HIV tests during the past 6 months.

These outcomes reflect the principle that optimal HIV care exists across a continuum, from timely diagnosis and linkage to care, to initiation of ART, and sustained adherence and retention in care over the life course [34]. They were selected because they have been identified as key quality improvement metrics by Vivent Health for all of its clinical sites. Missed visits are a marker of vulnerability for disengagement from care [35] and may predict loss of viral suppression [36] and subsequent mortality [37]. Viral suppression is the key indicator of a successful response to ART in all HIV care settings. Minimizing viral nonsuppression is, therefore, a main goal of national and global HIV elimination strategies [38].

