### Analytic Strategy: Effectiveness and Maintenance

In the stepped-wedge design, each site functions as its own control or usual care group before the implementation of ART-C. During this period, clinics treat patients with HIV using existing, standard treatment protocols and do not yet have access to the Connections app. To characterize intervention effectiveness, we will model site, time, and intervention status as predictors of primary outcomes using a repeated measures model to control for clustering by individuals and sites [47]. An indicator variable for intervention status will be modeled as 0 before intervention and 1 after ART-C is rolled out at each site. Random effects will be used to model the correlation between individuals within the same cluster (ie, site) in the stepped-wedge design. For a design with 8 clusters, 5 time points, and N individuals sampled per cluster per time interval, Y_ijk_ will be the response corresponding to individual k at time j from cluster i (i in 1,..., 7; j in 1,..., 8; k in 1,..., N) and Y_ij_ will be mean for cluster i at time j:

Y_ij_ = µ+ α_i_ + β_j_ + X_ij_θ

In this equation, α_i_ is a random effect for cluster i, β_j_ is a fixed effect corresponding to time interval j, X_ij_ is an indicator of the treatment status in cluster i at time j (1=intervention; 0=control), and θ is the treatment effect. The individual-level responses of no-show rates and viral suppression are binary, so the cluster-level responses Y_ij_ are proportions with variance σ_ij_^2^_e_ = µ_ij_ * (1 – µ_ij_). A variance inflation factor of 1 + (N – 1) ρ is incorporated into the analysis, where ρ is the intraclass correlation coefficient between individuals within the same cluster. Logistic generalized estimating equation (GEE) models will be determined using R statistical software (version 4.3.3; R Foundation for Statistical Computing) with geeglm (family=binomial) [48].

After establishing the base model, we will include potentially confounding and moderating factors by adding covariates, interaction terms, and weighting methods to the models. Potential clinic-level confounders will include the racial and ethnic categories, gender, age, and diagnosis of a SUD.

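### The model relating app use to missed visits and nonsuppression does not state that use comes before the outcome, nor adjust for the patient's own earlier outcomes, so its association could be confounded in either direction

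*Protocol article*

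**What the plan says.** All references are to the protocol article.

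- **The analysis.** Analytic Strategy: Reach, Adoption, and Implementation states: "Adoption will also be examined as a predictor of individual-level effectiveness outcomes for patients who enroll in the app using logistic GEE models". It names the outcomes ("outcomes: viral nonsuppression and missed visit") and then one further modelling feature: "Models will account for repeated measures using hierarchical clustering for repeated observations from patients within sites".
- **The exposure.** Data Collection defines patient-level adoption as "a patient accessing any part of ART-C beyond the home page during a given week in the 12-month period after downloading the app".
- **The outcomes.** Study Outcomes defines nonsuppression as a proportion "among those who received 1 or more HIV tests during the past 6 months". That definition is for outcomes examined at clinic level. The adoption section does not say whether the same look-back applies to individuals.
- **Known predictors.** The Introduction, in the section on just-in-time strategies, refers to "the tendency for patients to miss appointments during periods of greatest vulnerability" and says that "previous treatment disengagement and virologic nonsuppression are 2 strong predictors of future care disengagement".
- **Adjustment elsewhere.** Analytic Strategy: Effectiveness and Maintenance says that confounders and moderators will be handled "by adding covariates, interaction terms, and weighting methods to the models". This concerns the stepped-wedge model. The confounders named there are race and ethnicity, gender, age and substance use disorder diagnosis. Earlier missed visits and viral load are not among them.

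**The concern.** Patients choose how much they use the app, so this model compares self-selected heavier and lighter users within the enrolled group. Two things can produce an association without any effect of the app.

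1. **Order.** Use is recorded weekly for a year after download, and visits and viral load tests occur during that same year. Unless use is measured before each outcome, use that fell after a missed visit or a viremic test can be counted as predicting it. A bad period that both lowers use and causes a missed visit has the same result.
2. **Stable differences between patients.** Patients who were well engaged before enrollment may use the app more and also do better. The Introduction supplies half of this argument by naming earlier outcomes as strong predictors.

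Clustering by patient and site gives suitable standard errors. It removes neither problem.

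What is at stake is limited but real. This is the only individual-level analysis in the article that links app use to clinical outcomes, so its result bears on whether use appears to matter.

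**Working it through.** **The plan's own figure.** The article gives no figure for this model. Its only power figure concerns the stepped-wedge comparison. With 3682 patients and a design effect of 3.0, n per arm is 3682/3.0/2 = 613.7. For 26.7% versus 16.7%, two-sided alpha 0.05 (assumed, since it is not stated):

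- null SE = sqrt(2 × 0.217 × 0.783 / 613.7) = 0.02353
- alternative SE = sqrt((0.267 × 0.733 + 0.167 × 0.833) / 613.7) = 0.02336
- z = (0.10 − 1.96 × 0.02353) / 0.02336 = 2.31, so power is 98.9% against the stated 98.5%

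The same calculation for a 7-point reduction gives 82.8%, consistent with the stated figure above 80%. Nothing below alters these numbers.

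**Check 1: a two-state calculation for missed visits, app effect zero.** All inputs are assumptions. A patient is vulnerable for 30% of the time. Use occurs in 30% of vulnerable weeks and 60% of other weeks. Visits are missed with probability 0.55 and 0.20 respectively. Given the state, use and missing are independent.

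- Use and missed: 0.3 × 0.3 × 0.55 + 0.7 × 0.6 × 0.20 = 0.1335
- Use and attended: 0.51 − 0.1335 = 0.3765
- No use and missed: 0.3 × 0.7 × 0.55 + 0.7 × 0.4 × 0.20 = 0.1715
- No use and attended: 0.49 − 0.1715 = 0.3185
- Odds ratio = (0.1335 × 0.3185) / (0.3765 × 0.1715) = **0.66**

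The overall missed proportion is 0.1335 + 0.1715 = 30.5%, inside the 21.23% to 41.13% range across clinics in Table 2. Varying the inputs (vulnerable 30–50% of the time, missing 0.45–0.55 versus 0.20–0.25) gives 0.63 to 0.85 for use of 30–40% versus 60%, and 0.46 to 0.67 for 20% versus 70%.

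Now exchange the use rates, so that vulnerable patients use the app in 60% of weeks and others in 30%. The four cells become 0.141, 0.249, 0.164 and 0.446, and the odds ratio is (0.141 × 0.446) / (0.249 × 0.164) = **1.54**. The direction follows from an assumption that the documents do not settle.

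**Check 2: simulation for nonsuppression, app effect zero.** Taken from the article: 631 patients, 8 sites, 26.7% nonsuppression. Assumed: 4 quarters, mean use in 40% of weeks, 4 pre-enrollment results per patient, and an engagement trait and a use propensity each with SD 1 on the logit scale and correlation r. The fit is logistic GEE clustered by patient with site terms, 100 replicates per row. Cells give the odds ratio for 0 to 100% of weeks used, then the share of replicates that were significantly protective.

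| Scenario | Same quarter, unadjusted | Same quarter, prior results adjusted | Use one quarter earlier, unadjusted | Earlier and adjusted |
|---|---|---|---|---|
| r = 0 | 0.972, 5% | 0.976, 5% | 0.978, 4% | 0.985, 3% |
| r = 0.1 | 0.725, 32% | 0.812, 16% | 0.710, 28% | 0.793, 18% |
| r = 0.2 | 0.546, 78% | 0.688, 41% | 0.558, 63% | 0.702, 26% |
| r = 0.3 | 0.406, 95% | 0.568, 75% | 0.405, 96% | 0.566, 63% |
| r = 0.5 | 0.208, 100% | 0.353, 100% | 0.208, 100% | 0.355, 98% |
| r = −0.2 | 1.864, 0% | 1.492, 0% | 1.894, 0% | 1.519, 0% |
| r = 0, shared bad quarter (shock SD 0.5) | 0.528, 90% | 0.506, 93% | 1.023, 1% | 1.023, 1% |

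With 100 replicates, the Monte Carlo standard error of a share is at most sqrt(0.25/100) = 5 percentage points.

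On the risk scale, at r = 0.3 nonsuppression in the low, middle and high thirds of use is 32.0%, 26.4% and 21.5% with an inert app. Standardizing to the 4 prior results narrows this to 29.7%, 26.6% and 23.5%.

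The two remedies act on different problems. Ordering removes the bias from a shared bad quarter and does almost nothing for stable differences. Adjustment for prior results reduces stable differences and does nothing for the shared quarter. Together they still leave 63% falsely protective results at r = 0.3.

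**The case against.** The strongest reply is that the article is silent here and has not made a wrong choice. One sentence in a condensed article says that adoption will be examined as a predictor; lags and covariates for a supporting model are often left to a fuller plan. That largely stands. A reader might infer that the article specifies a concurrent, unadjusted model, or that it will present the association as an effect of dose. It says neither. The 6-month look-back comes from a clinic-level definition, so it cannot be assumed to govern this model.

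A reader might also infer that an inert app would necessarily show a protective dose-response. The documents do not support that. They report no relation between app use and engagement in care. The weekly check-in surveys ask about barriers and can lead to staff contact, so patients in difficulty might use the app more, and the sign would then reverse. The Introduction links vulnerability to missed appointments, not to app use.

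It is also right that two full years of EHR history cannot be assumed for every enrollee. The eligibility criteria set no minimum time in care, and recruitment lists are renewed quarterly.

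What survives is that the article does commit to the exposure, the outcomes, the enrolled population and the model family, and the single protection it adds does not address order or confounding. A better version is available at almost no cost.

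**Conclusion.** The point holds as an inexpensive improvement to a supporting analysis. As described, the adoption model does not ensure that use precedes the outcome and does not adjust for the patient's own earlier outcomes. An inert app could, and plausibly would, show a protective association if use tracks engagement even modestly: odds ratio 0.73 at a correlation of 0.1, 0.55 at 0.2 and 0.41 at 0.3. There is no association at zero correlation, and it reverses to 1.86 at −0.2. These sizes rest on the assumed correlation, trait variances and use rates; only the 631 patients, 8 sites and 26.7% come from the article. The stepped-wedge comparison, its estimate and its power are unaffected.

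**What to change.** State the following for this model, before analysis:

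1. **Order.** Measure meaningful use in a window of fixed, prespecified length that closes before each outcome: before each scheduled visit for missed visits, and before each viral load test for nonsuppression.
2. **Earlier outcomes.** Adjust for the patient's available pre-enrollment missed-visit proportion and nonsuppression from the EHR, with an indicator for patients with little history.
3. **Outcomes after download.** Do not adjust for them in the main version, since earlier use may have affected them. If wanted, do so as a sensitivity analysis.
4. **Reporting.** Present the result as an association with residual confounding, and keep causal claims to the randomized stepped-wedge comparison. The simulation shows why this is needed even after steps 1 and 2.

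The cost is small. App use and EHR outcomes are already being collected, so this is a change of analysis wording and some data preparation. Outcomes very soon after download drop out of this one model, and adjustment is weaker for enrollees with short histories.
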